## Abstract

Informal caregivers are those who provide unpaid care to a relative or friend with a chronic illness, disability or other long-lasting health or care need. Providing informal care in the context of chronic health conditions presents a significant global challenge. Examination of the determinants of informal caregivers’ behaviour, especially in terms of motivations and willingness to provide/receive care, is crucial to understanding the nature of caregiver and care recipient experiences. A large group of international researchers have co-operated to execute the ENTWINE iCohort-a multinational, transdisciplinary, longitudinal study incorporating intensive methods to examine caregiver experiences in the context of chronic health conditions. The aim of ENTWINE-iCohort is to investigate the broad spectrum of factors, i.e., cultural, personal, geographical, relational, psychological, and economic that may affect motivations, willingness to provide or receive care, among diverse groups of informal caregivers and their care recipients, in different countries that have different care systems. Study questionnaires will be disseminated on-line in nine countries: Germany, Greece, Ireland, Italy, Israel, the Netherlands, Poland, Sweden, and the UK. Cross-sectional and longitudinal multivariate analysis, including intensive longitudinal and dyadic data analysis will be applied to examine the relative contribution of the above factors to caregiver or care recipient wellbeing.

## 1. Introduction

Due to medical advancements and the subsequent rise in longevity worldwide, societies everywhere are facing a growing ageing population with an increase in those living with chronic, often disabling health conditions. However, in spite of this, many countries, such as the United Kingdom, The Netherlands and Italy, have seen a decline in spending on social care over the past decade [1,2]. Although investment has taken place more recently adult social care is considered to be in crisis and a significant funding gap exists [1,2]. Whilst investment in social care services fails to meet demand, families are required to manage care more informally, with the burden of care typically falling to female family members [3,4]. This continuing gender imbalance is in spite of an increased percentage of women who are also in paid employment [5,6]. This means that where the needs of older/ill individuals for long-term care is rising, the availability of informal caregivers is in decline. Known as the “Care Gap”, this will create huge problems for the sustainability of global health care systems that rely heavily on the provision of informal care. Thus, a multinational analysis of informal caregivers’ willingness to care and putative determinants of it as well as of informal caregivers’ wellbeing and other outcomes is essential for informing care solutions and public policy. 

A large group of international researchers have co-operated to execute the ENTWINE iCohort—a multinational, transdisciplinary longitudinal study incorporating intensive methods to examine caregiver experiences in the context of chronic health conditions. This paper presents the study protocol.

An informal caregiver for ENTWINE purposes is defined as a family member or friend who adopts a caring role for a person with a chronic health condition, disability, or other care need where needs require the caregiver to perform tasks beyond those typical of their usual role/relationship.

Research has commonly identified love and affection as the primary motivation for adopting a typically unpaid caregiver role [7,8] along with motives of duty and reciprocity [9]. However the complexity of dyadic relationships and attachments [10,11,12,13,14], the existence of varying cultural norms, values and obligations [15,16], competing social and economic demands on potential caregivers [17] and the fact that modern families tend not to be as geographically co-located as in previous generations [18,19,20,21,22] are less typically examined in relation to their influence on caregiver motivations. We face major challenges if we are to meet the demand for care (including informal care) across Europe on a societal (and often familial) assumption of family member willingness to adopt a caregiving role in the home or community. There is a real risk that the numbers experiencing negative physical and mental wellbeing as a consequence of caregiving [23,24,25,26,27] will increase and/or that the willingness to care will subside as people are expected to work for longer [28,29,30].

If informal care is to be maintained and supported, we need to better understand the range of factors—personal, interpersonal, social, economic, and geographic—that may influence caregiver willingness and motivation to adopt and maintain this demanding role or which may mitigate against negative care outcomes. The evidence gap that this study seeks to address will be informed by data from multiple countries facing similar ageing demographics but with different cultural and social norms around illness and care, and different care systems. Such understanding is important to the creation of culturally relevant policy and practice.

### 1.1. Primary Objective

To examine the current experience of caregiving, motivations to care and influences thereon among a diverse group of informal caregivers recruited by means of an intensive longitudinal cohort study (ENTWINE-iCohort) conducted in the five countries represented in the ENTWINE Consortium network (UK, Ireland, The Netherlands, Italy and Israel) plus four other EU countries (Germany, Greece, Poland, Sweden).

### 1.2. Secondary Objectives

To conduct a full examination of the:

Determinants of, and cultural differences in, motivations and willingness to provide care with specific attention paid to the contribution of personal values and meanings attached to illness and caregiving and their impact on caregiver outcomes,

Personal and geographical barriers and facilitators of caregiving with specific attention paid to the contribution of caregivers’ personality traits and geographic distance from the care recipient upon willingness to care and caregiver outcomes,

Diversity in experiences of caregiver—care recipient dyads, with specific attention paid to the characteristics of the dyads, interpersonal processes, willingness to provide and receive care and individual and relational outcomes.

Patterns of and differences across countries in informal care costs, as well as the preferences for, and use of, formal versus informal caregiving, and the personal and contextual influences thereon.

Characteristic of access to, use of and challenges of household-based migrant care work and how this supports informal caregiving

Each of these objectives is addressed in detail by one early stage researcher (five in total), each under supervision of two senior academics, and with oversight held by a Work Package Lead and ENTWINE management team.

Have a caregiver declaration regarding care recipient cognitive and physical capacity to complete questionnaires online;

Have access to the Internet.

## 3. Recruitment Methods

Caregivers and care recipients are invited to participate jointly in the intensive longitudinal cohort study, but caregivers are encouraged to participate even where the care recipient is unable/unwilling to participate.

Recruitment will be either by (1) broad-based online recruitment via academic, social and news media and care or patient relevant organisations or (2) a more targeted, direct approach via user groups, carer organisations and primary and secondary care settings using advertising (poster displays, flier distribution) and direct face-to-face contact (due to COVID-19 restrictions direct face-to-face recruitment was not initiated). For recruitment method 1 a multi-language advertisement/flier was produced for all included study sites inviting adults who meet the aforementioned eligibility (inclusion) criteria to, for example,

“Take part in an international study of caregiving—find out more at this URL for ENTWINE iCohort survey link” (see Supplementary File S1).

These fliers shall be distributed in each country via national and international charity organisations specific to our target conditions, e.g., Alzheimer’s Society, Stroke Association, Eurocarers (and national equivalents) and, subject to local approvals, also displayed in public venues such as community pharmacists, health, leisure, or educational centres.

The flier/advertisement will direct potential caregiver participants to the online platform for the ENTWINE-iCohort where they can register and access an eligibility survey (Supplementary File S11), a full Participant Information Sheet (PIS, Supplementary File S2) and electronic consent (Consent Form, Supplementary File S3) shall be required before the caregiver survey (baseline or follow-up, or the intensive longitudinal component, Supplementary Files S4, S6 and S8) can be accessed.

The caregiver (CG) shall be invited to consider whether they wish to nominate their care recipient (CR) to take part in the parallel Care Recipient Survey (baseline or follow-up, or the intensive longitudinal component, Supplementary Files S5, S7 and S9) and if so they shall direct them to the relevant registration site where they can access the CR survey tool for independent completion. CRs who self-identify will also be directed to the relevant registration site to access the CR survey tool. Both CG and CR will also be asked to indicate willingness to be contacted for a future related research study (Supplementary File S10).

## 4. Questionnaire Randomisation

Caregivers: the questionnaire for the CG is divided into four modules (Note that the economic, employment and migrant care work sub-components were combined into one module although this addresses the work of 2 ESRs), that is a core module and one module for variables that are specific for each sub-study (1 = cultural aspects; 2 = personality and geographical barriers; 3 = interpersonal processes; 4 = employment and costs including migrant care work). The core module includes personal and demographic information, care context and care task information, willingness to care and wellbeing outcomes (affect, gains, burden). In addition to the core module, participants will randomly receive two other modules (see Figure 1) as programmed within Questback.

This process will reduce the burden for participants and ensures that drop-out and missing values do not centre on specific modules (i.e., if a module is always offered last, this could increase the chance of missing data for this specific module).

Care recipients. The questionnaire for the CR is much shorter and the same for all CRs i.e., there are no modules.

## 5. Sample Size Calculation

Whilst each specific ESR project has its own objectives (as described above), three are addressing those in relation to the primary outcomes of willingness and motivations to care. Given the number of variables to be assessed (see Measures, approximately 30 variables will be used in total) it is our intention to recruit CGs to the case: variable ratio of 10:1, i.e., 300 CGs per country. For CRs, who are assessed on fewer variables, we expect at least 150 participants per country—anticipating that at least 50% of our sample of 300 CGs per country will identify an eligible care recipient (based on our previous research). Analyses will be appropriate to the attained sample size on study completion in order to achieve satisfactory statistical power.

The a priori sample size calculation was informed by previous research. Achieving 90% power to detect a medium sized association/ explained variance R^2^ = 0.25, with entry of up to 10 independent variables (randomly selected variables dependent on prior analyses) and willingness to care (measured as a continuous variable) in a multivariate regression analysis with an alpha of 5% (G*Power 3.1, [31]).

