## 7. Analysis Plan

Five separate studies are addressed, and each will use selected variables from the Core survey, plus module-specific items. For each study, baseline data will first be analysed for the full sample, with a smaller sample entering longitudinal analysis dependent on completing both timepoints of the survey. The analysis plan will evolve depending on our a priori set of research questions, as well as the sample characteristics and final sample size.

*Missing data handling.* Prior to analysis the data set will be cleansed and checked for missing data. Missing data are a critical challenge when dealing with online surveys thus the ENTWINE iCohort survey will employ multiple checkpoints to address this. In the cases where missing data exist, a descriptive analysis of the missing data, as well as a number of hypothesis tests, will be carried out to determine the mechanism of missingness. These tests include Little’s test and Fairclough’s logistic regression method [59,60]. If data are missing completely at random (MCAR), missing values will be subjected to list-wise deletion and complete case analysis will be performed. If data is missing at random (MAR), we will adopt a hot deck imputation for variables with a negligible proportion of missing values (i.e., less than 5%) and multiple imputations by chained equations (MICE) for variables with a larger proportion of missing values [61,62,63,64].

For all analyses, assumptions regarding multicollinearity, singularity, normality, linearity, and homoscedasticity will be tested.

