## 9. Dissemination

A dissemination strategy has been prepared by the ENTWINE WorkPackage group and our Dissemination and Website Taskforce. This will include dissemination to both academic and non-academic stakeholders in health, public health and social care sectors by means of conference presentations, blogs and multi-media news items on our study website, and preparation of a newsletter providing an executive summary of study findings and their implications.

**Study status**-Baseline recruitment to 31 August 2021; recruitment figures 2736 recruited, 1834 completers (1120 full completion) with follow-up ongoing.
Ireland 14/08/2020–31/05/2021UK 14/08/2020–31/05/2021Poland 14/08/2020–31/05/2021Italy 25/08/2020–31/05/2021Netherlands 16/10/2020–31/05/2021Sweden 23/10/2020–31/05/2021Greece 31/10/2020–31/05/2021Israel 16/02/2021–31/08/2021Germany 17/02/2021–31/08/2021

Participants were invited to take part in the follow up assessment 181 days after the initial baseline invitation. Data collection completed for all countries on 15 December 21; 6 month follow-ups were not offered to participants who completed baseline data after 31 May 2021 due to project funding deadline restrictions.

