## Figures and Tables

**Figure 1 ijerph-19-00821-f001:**
[figure not shown]
Questback randomization process. Note: 1 = cultural and psychosocial aspects; 2 = personality and geographical barriers; 3 = interpersonal processes; 4 = employment, costs and migrant care work.

**Table 1 ijerph-19-00821-t001:** Summary of measures.

Section/Measure	Description and Max*N of Items	Scoring	IV, DV, Mod, Med	CG Baseline	CG Follow Up	CR BASELINE	CR Follow Up

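### The 10:1 ratio behind 300 caregivers per country holds only for core variables: on average 150 per country answer any one module

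*Protocol article*

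**What the plan says.** Three parts of the protocol article bear on this.

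- **Section 5 (Sample Size Calculation)** refers to the Measures section, says that "approximately 30 variables will be used in total", and concludes that "it is our intention to recruit CGs to the case: variable ratio of 10:1, i.e., 300 CGs per country". A separate sentence gives a power basis: 90% power, R² = 0.25, up to 10 independent variables, alpha 5%, with willingness to care as a continuous outcome. It states no resulting n. Neither sentence mentions the modules.
- **Section 4 (Questionnaire Randomisation)** lists the non-core modules as "1 = cultural aspects; 2 = personality and geographical barriers; 3 = interpersonal processes; 4 = employment and costs including migrant care work" and states: "In addition to the core module, participants will randomly receive two other modules". Table 1 has the same layout, a core block and Modules 1 to 4.
- **Section 7 (Analysis Plan)** says of the five studies that "each will use selected variables from the Core survey, plus module-specific items". It then says: "For each study, baseline data will first be analysed for the full sample".

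The article gives no expected number of caregivers per module or per pair of modules.

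**The concern.** The ratio divides all caregivers in a country by all variables in the survey. That works only if every caregiver supplies every variable. Under the module design no caregiver does: each one skips two of the four modules by randomisation. So the denominator counts variables from the core and all modules, while the numerator counts people who answered only part of them.

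The analysis text repeats the mismatch. Every study is to use module-specific items, yet the baseline analysis set is described as the whole sample.

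As written, a reader would credit a model containing module items with twice the caregivers it is planned to have. Three of the projects address willingness and motivations, and many of their distinctive predictors (values, personality, geography, interpersonal processes) sit in Modules 1 to 3. The stated ratio is therefore least accurate where those projects add something to the core.

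**Working it through.** **Inputs.** From Section 5: 300 caregivers per country, about 30 variables, 10:1; and for the power clause R² = 0.25, 10 predictors, alpha 0.05, power 90%. From Section 4: four non-core modules, two given to each caregiver. From Section 1.1: nine countries (five plus four). Assumption, used only where stated: the six module pairs are equally likely. Figure 1 ("Questback randomization process") is not visible in the text at hand, so the allocation weights cannot be confirmed.

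**1. The plan's own figure.** 30 variables × 10 = 300. It reproduces exactly.

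**2. Caregivers per module.** 300 caregivers × 2 modules = 600 module completions. Over four modules, 600 / 4 = 150 on average. This average does not depend on the weights: if one module gets more than 150, another gets fewer. With equal weights each module has 150.

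**3. Caregivers per pair.** There are C(4,2) = 6 pairs, so 300 / 6 = 50 on average. For any given pair, 50 requires equal allocation.

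**4. Three or four modules.** Zero, by the two-module rule alone.

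**5. Pooled.** 9 × 300 = 2700; 2700 / 2 = 1350 per module; 2700 / 6 = 450 per pair.

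**6. What 10:1 supports.**

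| Variables drawn from | Planned n per country | Variables supported at 10:1 | Planned n pooled |
|---|---|---|---|
| Core only | 300 | 30 | 2700 |
| Core + one module | 150 | 15 | 1350 |
| Core + two modules | 50 | 5 | 450 |
| Core + three or four modules | 0 | none | 0 |

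Thirty variables on one module's caregivers give 150 / 30 = 5:1 per country. Pooled, they give 1350 / 30 = 45:1. These are complete-case counts and assume that all 300 answer both modules they are given.

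**7. The power clause.** The overall F test of R² = 0 has 10 and N − 11 degrees of freedom and noncentrality f² × N, where f² = R² / (1 − R²) = 0.25 / 0.75 = 0.333.

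| Effect size | N for 90% power | Power at N = 150 | Power at N = 50 |
|---|---|---|---|
| R² = 0.25 (f² = 0.333) | 72 | 99.97% | 69.9% |
| 0.25 read as f² | 92 | 99.5% | 54.6% |
| f² = 0.15 (assumed conventional medium effect) | 147 | 90.9% | 32.6% |

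The article calls its effect medium but states R² = 0.25, so the last two rows show the range of readings. A 10-predictor model on one module keeps 90% power at the planned 150 under all three. It would not at 50.

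**The case against.** Much of the case on the other side stands.

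- **The power clause concerns a smaller model.** It allows up to 10 predictors. At 150 that is 15:1, and about 72 caregivers are needed. This stands. A reader might infer that no module-specific model meets the stated ratio, but any model with 15 or fewer variables does so per country.
- **Thirty is a total across the survey.** Section 7 has each study select variables from the core and add its own module's items, and Table 1 gives each module only four to six caregiver measures. This stands, although subscales raise the count. No 30-variable model is announced. What fails is the rationale for 300, which rests on that total.
- **No cross-module model is specified.** This stands. The moderation examples in Section 7.1 can be met from the core plus one module. The figures of 50 and zero apply to any model that does combine modules, not to one the article commits to.
- **No per-country module regression is specified.** This stands. A reader might infer over-fitted country models with unstable coefficients, but that depends on an analysis the article does not state, and the pooled module n is 1350. Still, the ratio is itself expressed per country, so it should be correct on that basis.
- **The outcomes are core.** This stands. The Willingness to Care Scale and the two motivation scales go to every caregiver.
- **The full-sample wording contrasts baseline with the smaller follow-up sample.** That is a fair reading of its purpose, but the sentence remains untrue of module items.

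A reader might also divide the recruitment counts under Study status in Section 9 by country and module to show a further shortfall. The article does not split those counts into caregivers and care recipients or by country, and it does not define its two completion categories. Per-country module figures cannot be derived from them.

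**Conclusion.** The point holds as a misstated property of the sample size. Section 5 presents 10 cases per variable for about 30 variables at 300 caregivers per country. Under Section 4 that ratio is available only for core variables. For variables from the core plus one module, the same 300 gives 150 on average, which halves both the ratio and the number of variables it supports. The analysis-set wording in Section 7 has the same fault.

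The average of 150 and the zero for three or more modules follow from the two-of-four rule alone. Exactly 150 for each module and 50 for each pair also require equal allocation.

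The consequence is limited. It is not a general loss of power: the stated power clause survives for a single-module model at the planned n, and the willingness and motivation outcomes are planned for all caregivers.

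**What to change.** **Section 5.** State that 300 per country and 10:1 apply to models using core variables only. Add the planned n and ratio for the other two cases:

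- core plus one module: 150 per country, 1350 pooled, about 15 variables per country at 10:1;
- any model combining two modules: about 50 per country, 450 pooled, about 5 variables per country at 10:1, under equal allocation.

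State the allocation weights, or confirm that pairs are equally likely. Add that no caregiver supplies complete data on three or more modules.

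**Section 7.** Replace the full-sample wording with: *all baseline caregivers for core variables, and caregivers randomised to that module for module-specific items*.

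**Cost.** Wording only, and a less favourable stated ratio for module models. No new participants and no change to the questionnaire or the randomisation.

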## 6. Measures

Table 1 presents all measures used within the ENTWINE iCohort survey, with a brief description of the concept addressed, timings of use, and whether they reflect a key outcome measure (DV) or an IV/potential mediator or moderator variable. Wherever possible, validated instruments were employed, and short-form assessments were preferable where available in order to reduce participant burden.

Measures that are not validated and available in the required language will be translated into the appropriate languages using accredited translators who will be native speakers of the target languages and fluent in English. Translations will be checked for compatibility with the original version in a process of back translation, also performed by persons who will be native in the foreign language and fluent in the English language, to ensure that none of the original meaning is lost. For each language, a potential research consultant/reviewer will be identified to ensure that any discrepancies between the forward and back translations can be resolved appropriately by discussion with the translators. All translations will be coordinated by one project partner to ensure consistency. Piloting in each country shall enable identification of any semantic inconsistencies.

